#### Perception and Acceptance

The students’ perception of the activity and their degree of satisfaction with the knowledge achieved will be assessed. Questions will evaluate the preparation level, nervousness, satisfaction, and acceptance of students regarding the proposed activities. These outcomes will be evaluated based on the State Trait Personality Inventory Scale [15]. Moreover, the goal of this outcome will verify if the students who participated in the laboratory training felt more prepared for the caries lesions detection in a clinical situation.

#### Retention of Knowledge and Skills

To evaluate the retention of knowledge and skills acquired after the tutored theoretical laboratory training, students who entered the university before the participating students will be interviewed for data collection, and these data will be used as control and compared with the trained group. This stage will be a nonrandomized phase of the study, nested in the main study. To compare the long-term outcomes, a theoretical and practical assessment will be applied to participating students after 1 or 2 years following the first training and compared with a class in the same year of the undergraduate program, but who had not been exposed to this methodology. This stage of study will be adjusted considering the curriculum of each center in accordance with the course subjects offered in the periods of interest. The flowchart of the study design is summarized in Figure 2.

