## Methods

### Ethical Aspects

The Research Ethics Committee of all institutions involved previously approved this protocol. The participants will receive and sign an informed consent prior to their involvement in the research. For ethical reasons, the students allocated to the theoretical group will receive laboratory training at the end the outcome assessments. Participant confidentiality will be ensured using identification code numbers. Participant identifiable information will be stored in locked filing cabinets in a secure room.

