### Statistical Analysis

For the theoretical evaluation, total number of correct responses for test and control groups will be compared at both times of evaluation (immediate and long term). Data from the number of correct responses per question will be submitted to analysis, also considering the question as a factor.

For the practical assessment, performance-related parameters (sensitivity, specificity, accuracy) when using the visual method for the caries detection and evaluation of lesions activity will be calculated. These values will be compared between groups using multilevel analysis, considering both experimental groups and different centers.

The scores given by students for acceptance and perception of the activities carried out will be compared between groups. Regression analysis will be used in each experimental group to verify the association between student performance in caries lesions detection versus theoretical knowledge and student perception in relation to the activity. Baseline student knowledge and willingness to learn caries detection will be considered during these analyses.

The association between the results of immediate theoretical and practical assessments with knowledge and skills retained in the long term will be assessed.

For all analyses, a multilevel approach will be used to consider different levels explored. The assessment, the student, the center, and the country could be considered as possible levels for these analyses considering the possible clustering observed for centers and, eventually, countries. For all the parameters tested, the influence of the different centers and the level in the course (first or end years) will be investigated by regression analysis. The significance level will be set at 5%.

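### Long-term comparison: exposure varies only between entry classes within a center, but class is not among the model levels named, so a model limited to those levels would understate the standard error

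*Protocol article*

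**What the plan says.** All references are to the protocol article.

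- **Comparator.** Under Retention of Knowledge and Skills, "students who entered the university before the participating students will be interviewed for data collection" to serve as controls. The stage is openly labeled: "This stage will be a nonrandomized phase of the study, nested in the main study".
- **Timing and contrast.** In the same section, "a theoretical and practical assessment will be applied to participating students after 1 or 2 years following the first training", and the results are "compared with a class in the same year of the undergraduate program, but who had not been exposed to this methodology".
- **Randomized controls.** Ethical Aspects says that "the students allocated to the theoretical group will receive laboratory training at the end the outcome assessments".
- **Model.** Statistical Analysis applies a multilevel approach to all analyses: "The assessment, the student, the center, and the country could be considered as possible levels for these analyses". The reason it gives is clustering by center and possibly by country. For all parameters, "the influence of the different centers and the level in the course (first or end years) will be investigated by regression analysis". Significance is set at 5%.

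Class or entry cohort is not named as a level, a source of clustering or a regression term.

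**The concern.** Two untrained classes at the same school will rarely have exactly the same mean score, because intake, lecturers, timetable and curriculum change from year to year. In the retention phase one class is trained and the other is not, so this variation falls directly on the training contrast. A center or country intercept removes only what the two classes share. A model with only those intercepts treats students in different classes of one center as independent. It therefore tests whether these particular classes have equal means, when the question is whether training has a lasting effect.

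No other named term fills the gap. Course level is the same for both classes, because they are matched on program year. The center characteristics are shared by both classes. Adjusting this stage to each center's curriculum adds no variance component.

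The comparison matters because the Results section expects the benefit mainly in long-term retention.

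**Working it through.** The article states no sample size, power or ICC, so there is no figure of its own to reproduce. Only the nominal 5% can be tested.

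**Inputs from the article:** 5% significance (taken as two-sided; sidedness is not stated); 16 centers (7 + 9); an untrained comparison class in the same program year; levels named without class.

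**Assumptions, not in the article:** one trained and one untrained class of m students per center; m = 20, 40 or 60; ICC for class within center from 0 to 0.10; a continuous outcome with total within-center variance 1; no true effect.

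**Step 1. Variance of the training contrast.** With K centers, the mean within-center difference has true variance (2/K) × [ICC + (1 − ICC)/m] = (2/(Km)) × [1 + (m − 1) × ICC]. A model with no class term uses about 2/(Km). The ratio is

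DEFF = 1 + (m − 1) × ICC.

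K cancels, so adding centers leaves the inflation unchanged.

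**Step 2. Actual type I error** = 2 × [1 − Φ(1.96/√DEFF)]. For m = 40 and ICC 0.05: DEFF = 1 + 39 × 0.05 = 2.95; 1.96/√2.95 = 1.14; error = 25.4%.

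| ICC | m = 20 | m = 40 | m = 60 |
|---|---|---|---|
| 0 | 5.0% | 5.0% | 5.0% |
| 0.01 | 7.2% | 9.6% | 12.0% |
| 0.02 | 9.5% | 14.2% | 18.4% |
| 0.05 | 16.0% | 25.4% | 32.4% |
| 0.10 | 25.0% | 37.6% | 45.6% |

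**Step 3. Simulation check** (20,000 null trials per setting; center plus exposure, student-level residual, 2Km − K − 1 degrees of freedom). With 16 centers:

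| ICC | m = 20 | m = 40 | m = 60 |
|---|---|---|---|
| 0 | 5.3% | 5.2% | 5.1% |
| 0.01 | 7.0% | 9.3% | 12.1% |
| 0.02 | 9.9% | 14.6% | 18.6% |
| 0.05 | 16.6% | 26.1% | 33.2% |
| 0.10 | 26.0% | 38.8% | 46.4% |

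With 7 centers at ICC 0.05 the results are 16.5%, 25.6% and 33.1%, which confirms that the number of centers hardly matters.

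**Step 4. Standard error ratio.** If the model's residual were purely within-class (variance 1 − ICC), the true standard error would be √[1 + m × ICC/(1 − ICC)] times the model's: 1.43, 1.76 and 2.04 at ICC 0.05 for m = 20, 40 and 60. The fitted residual also absorbs a little class variation. For K = 16, m = 40 it averages [2 × 16 × 39 × 0.95 + 15 × (40 × 0.05 + 0.95)]/1263 = 1229.85/1263 = 0.974, and the ratio is √(2.95/0.974) = 1.74.

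**Step 5. Class as the unit.** A paired t test on class means (K − 1 degrees of freedom) gave 4.7% to 5.3% in every simulated setting, with both 7 and 16 centers.

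**The case against.** The strongest reply is that the list of levels is permissive. It says what could be considered, it is not closed, and a condensed article may leave the exact random effects to a fuller plan. That stands: the article does not commit to the model simulated here. A random center-by-exposure effect would also do the work with one class pair per center, and the planned study of center influence does not rule it out, although it is not stated. The point survives in conditional form, because the article does name levels and sources of clustering, applies them to all analyses, and so includes one in which exposure varies only between classes.

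A reader might infer several stronger claims that the article does not support:

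- **That the 5% level is certainly broken.** This depends on the model finally used and on class variance above zero. At ICC 0.01 with 20 students per class, the error is only 7.2%.
- **That there is exactly one class pair per center, hence at most 16 pairs.** This is read from a singular noun. Experimental Groups enrolls two course levels, so a center might supply two pairs, and Study Design allows further centers. The mechanism is the same either way.
- **That the course-level effect is inflated to the same degree.** No calculation was run for it.
- **That the immediate comparison is affected.** It is not, because students are randomized within class.

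Statistical Analysis also says theoretical scores of test and control groups are compared at the long-term time point, and Ethical Aspects does not say which outcome assessments precede the controls' training. A comparison by randomized arm within class would not have this problem. The point concerns the trained-versus-untrained class comparison that the Retention section describes.

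**Conclusion.** The concern holds conditionally. For the trained-versus-untrained long-term comparison, the levels and clustering named omit the unit at which exposure varies. A model confined to them gives intervals that are too narrow and exceeds 5% whenever class variance is non-zero.

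The size rests wholly on assumed values. For 20 to 60 students per class, type I error is about 7%-12% at ICC 0.01, 9%-19% at ICC 0.02 and 16%-33% at ICC 0.05. The direction does not depend on those values; only ICC 0 leaves the level at 5%.

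**What to change.** In Statistical Analysis, for the long-term trained-versus-untrained comparison, name class (entry cohort within center) as a random effect between student and center, with degrees of freedom based on the number of classes. Where each center supplies one class pair, a random center-by-exposure effect serves equally, as does an analysis of within-center differences in class means with one value per pair. State how many course levels, and so how many class pairs, each center contributes.

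This takes a sentence or two and no new data. The cost is a wider interval. In the example with 16 pairs, 40 students per class and ICC 0.05, the standard error rises 1.74-fold and the critical value goes from 1.96 to 2.13 (15 degrees of freedom), so the interval is about 1.74 × 2.13/1.96 = 1.9 times as wide.

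The change corrects the error variance only. The comparators are always earlier entrants, so a systematic difference between earlier and later cohorts remains confounded with training. The plan should state this as a limit on the retention conclusion.

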**Figure 2 figure2:**
[figure not shown]
Study design and phases to be conducted.

### Center/Student Characteristics

Some characteristics related to each center will be collected during the planning and execution/data collection stages. In the planning phase, a structured questionnaire will be applied to the center coordinators in order to identify relevant aspects of center size/potential, curricula, human resources/faculty preparation, infrastructure/facilities, and expected difficulties for participant centers. Afterward, in the execution phase, we will first map each student’s background and willingness to learn Cariology and caries detection by a form they should fill out before the theoretical class. The student’s background will show both the student’s knowledge at baseline, and also the possible contents taught at his/her center. Second, qualitative research on topics and strategies used in teaching/learning of Cariology will be investigated among students and lecturers in different centers. These quantitative-qualitative variables will be used as independent variables related to the center in further analysis.

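### Each student's pre-class baseline is labelled a center-related variable and, on the plain reading, is not carried into the randomised efficacy comparisons; the wording is ambiguous, and precision, not validity, is at stake

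*Protocol article*

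**What the plan says.** **Collection.** Under Center/Student Characteristics, student background and willingness are captured "by a form they should fill out before the theoretical class". The section explains what this yields: "The student’s background will show both the student’s knowledge at baseline, and also the possible contents taught at his/her center". Under Experimental Groups, students and tutors learn the allocation only after the theoretical class. The form is therefore a student-level measure that knowledge of allocation cannot have influenced.

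**Declared role.** The same section also covers the coordinator questionnaire and the qualitative work on teaching. It closes with one statement for all of this material: "These quantitative-qualitative variables will be used as independent variables related to the center in further analysis".

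**Use in the analysis.** The Statistical Analysis section proceeds as follows:

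- Theoretical outcome: "total number of correct responses for test and control groups will be compared at both times of evaluation (immediate and long term". No baseline covariate is named.
- Practical outcome: "These values will be compared between groups using multilevel analysis, considering both experimental groups and different centers". Group and center are named; baseline is not.
- Perception scores and within-group regressions: this paragraph ends with "Baseline student knowledge and willingness to learn caries detection will be considered during these analyses".
- All parameters tested: "the influence of the different centers and the level in the course (first or end years) will be investigated by regression analysis". Center and course level are named; baseline is not.

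Decision-making is defined as an efficacy outcome under Cost Efficacy. In the Statistical Analysis section, only the general statements reach it.

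**The concern.** Prior knowledge of caries detection is a natural candidate to predict a post-class score in caries detection. It is measured on every participating student before allocation is known, so adjusting a randomised comparison for it is legitimate.

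Two features of the text work against that use. The declared role puts a student measurement among the center variables. The only sentence that calls it a student variable sits in a paragraph about perception and associations within each arm, not in the two paragraphs that compare efficacy between arms.

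If analysts follow this literally, the intervals for the main contrasts will be wider than the collected data allow. If they do not, the choice between adjusted and unadjusted efficacy results stays open while data are already accruing, as the Results section says they are.

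**Working it through.** **Plan's own figure.** There is none to reproduce. The article gives no sample size, power, effect size, standard deviation or baseline-outcome correlation.

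**Inputs from the article.** Sixteen centers; classes randomly divided into two groups; significance level 5%.

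**Assumed inputs.** 1:1 allocation, two-sided testing, a continuous outcome in a linear model, and r from 0.1 to 0.6. Here r is the correlation between a student's baseline and outcome within class, after center and course year are accounted for.

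**Step 1: a center-level value does not help.** Suppose the baseline is entered as a center value z, the same for every student in that center. With students divided 1:1 within each class, z has the same mean in both arms. It is uncorrelated with allocation and explains no within-class variation, so the variance of the arm contrast is unchanged. The student's own value does vary within class and can remove residual variance.

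**Step 2: simulation check.** The setting was 16 centers of 40 students (center size assumed), randomised 1:1 within center, true difference 0.2 SD, 1,500 repetitions. The table gives empirical standard errors of the arm difference.

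| r within center | center only | center-mean baseline | student's own baseline | ratio, own ÷ center only |
|---|---|---|---|---|
| 0.3 | 0.0784 | 0.0784 | 0.0744 | 0.949 |
| 0.5 | 0.0781 | 0.0781 | 0.0675 | 0.864 |
| 0.7 | 0.0811 | 0.0811 | 0.0565 | 0.696 |

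The center-mean version gave a ratio of 1.000 throughout. The mean estimate lay between 0.197 and 0.200 in all three models, so none showed material bias.

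**Step 3: size of the gain.** Variance factor = 1 − r². Standard error ratio = √(1 − r²). Equivalent increase in students = 1/(1 − r²) − 1. The power column takes a design with 80.1% power unadjusted (illustrative difference 0.2 SD, 393 per arm).

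| r | 1 − r² | variance reduction | SE ratio | equivalent extra students | power after adjustment |
|---|---|---|---|---|---|
| 0.1 | 0.99 | 1% | 0.995 | 1% | 80.4% |
| 0.3 | 0.91 | 9% | 0.954 | 10% | 83.6% |
| 0.5 | 0.75 | 25% | 0.866 | 33% | 89.9% |
| 0.6 | 0.64 | 36% | 0.800 | 56% | 93.9% |

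**Limit of the formula.** It holds for a linear model of a score such as total correct answers. It does not carry over directly to per-question analyses or to sensitivity and specificity fitted as binary item-level models.

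**The case against.** The strongest reply is that the article never rules baseline out.

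- The sentence saying baseline knowledge will be considered follows the theoretical, practical and perception comparisons, and its reference to the analyses could cover all of them.
- The multilevel approach is stated for all analyses, with the student among the possible levels. The Abstract says that center-related variables will serve for model adjustment.
- The label in the characteristics section is one loose sentence closing a section whose title names both centers and students. It does not say that student values will be averaged.
- Model-by-model covariate lists usually sit in a fuller plan, which is not shown.
- The form maps background and willingness and is not described as a scored pre-test. Classmates share a curriculum, so the within-class correlation may be low.

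Most of this stands. A reader might infer that the plan excludes baseline from the efficacy models, or substitutes center means for it; neither is stated. A reader might also infer that the efficacy results are biased or underpowered. Randomisation protects against bias, and ordinary chance imbalance is already reflected in the standard error. With no power target stated, no shortfall can be shown.

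The objection does not remove the point, because the point is about what is written. A student measurement is given a center-related role, and where the article names factors for the efficacy comparisons, baseline is not among them. The Abstract does not repair this: combined with that label, it would bring baseline in as a center descriptor, the version that Step 1 shows adds nothing.

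**Conclusion.** The point holds as a matter of ambiguous wording with a possible cost in precision. On the plain reading, the immediate theoretical, practical and decision-making comparisons do without a valid student-level covariate that is already collected. The group difference remains unbiased either way.

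For a linear model the forgone variance reduction is 1% at r = 0.1 and 36% at r = 0.6. The true size cannot be derived from the article and may be near the lower end. It rests on an assumed within-class r, 1:1 allocation within class and a continuous score. The change is worth making because it is free and settles the adjustment in advance, not because validity is threatened.

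**What to change.** 1. **Statistical Analysis.** State that each student's own baseline knowledge and willingness enter the immediate between-arm models for theoretical, practical and decision-making outcomes as prespecified student-level covariates. Include class (center by course year), within which students are randomised, as a stratum.
2. **Center/Student Characteristics.** Separate the two kinds of variable: center descriptors from the coordinator questionnaire and qualitative work on one side, and each student's form on the other. Center means of baseline may still be reported as context.

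The change is confined to the immediate, randomised comparisons. The long-term comparison is nonrandomised and uses other classes, for whom no pre-class form is described.

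**Cost.** Wording only, with no new data or procedures. It should be settled before outcomes are compared by arm.

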### Statistical Analysis

For the theoretical evaluation, total number of correct responses for test and control groups will be compared at both times of evaluation (immediate and long term). Data from the number of correct responses per question will be submitted to analysis, also considering the question as a factor.

For the practical assessment, performance-related parameters (sensitivity, specificity, accuracy) when using the visual method for the caries detection and evaluation of lesions activity will be calculated. These values will be compared between groups using multilevel analysis, considering both experimental groups and different centers.

The scores given by students for acceptance and perception of the activities carried out will be compared between groups. Regression analysis will be used in each experimental group to verify the association between student performance in caries lesions detection versus theoretical knowledge and student perception in relation to the activity. Baseline student knowledge and willingness to learn caries detection will be considered during these analyses.

The association between the results of immediate theoretical and practical assessments with knowledge and skills retained in the long term will be assessed.

For all analyses, a multilevel approach will be used to consider different levels explored. The assessment, the student, the center, and the country could be considered as possible levels for these analyses considering the possible clustering observed for centers and, eventually, countries. For all the parameters tested, the influence of the different centers and the level in the course (first or end years) will be investigated by regression analysis. The significance level will be set at 5%.

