### Experimental Groups

Undergraduate students at the beginning (up to second or third year) and the end of the Dentistry course (last 2 years) will be included. All students will be invited to participate, but only those who consent to participate will be included. The classes will be randomly divided into 2 groups. The randomization will be made by a central allocation located in the coordinating center, by sending the list of students to be invited. All students will be randomized, even those that will not participate. These losses will be computed and analyzed later.

One group (control) will be exposed to a 60- to 90-minute conventional theoretical class and the other group (test) will be exposed to the same theoretical class and a 90-minute laboratory class, including exercises and discussions based on the evaluation of a pool of images and extracted teeth. All students will attend the class together before the allocation. For the test group, the participants will be assigned in small groups (7-10 students) mediated by graduate tutors and/or teachers. Students will assess 30 clinical images and 10 teeth for severity (ICDAS scores) and activity status [14]. Tutors/teachers will work on correcting exercises and also discussion of questions raised by the group. In case of disagreement, tooth revaluation will be possible with the help of tutors/teachers so that students understand potential mistakes. For the control group, they will begin the outcomes assessment after having finished the theoretical class.

Despite the allocation, both groups will begin their activities (for training or outcomes assessment) at the same time, avoiding demotivation of any group. Students and teachers/tutors will know the allocated group only when they will be prepared for the activities after the theoretical class, guaranteeing the allocation concealment.

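### Separate regressions in each arm give no valid test of whether the link between detection performance and theory knowledge or perception differs by arm; one interaction model would supply it

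*Protocol article*

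**What the plan says.** In the Statistical Analysis section of the protocol article, the association analysis is fixed by arm: "Regression analysis will be used in each experimental group to verify the association between student performance in caries lesions detection versus theoretical knowledge", continuing "and student perception in relation to the activity". Two covariates are attached: "Baseline student knowledge and willingness to learn caries detection will be considered during these analyses". The significance level is 5%, with sidedness not stated.

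Two general statements in the same section could bear on this. The first is "For all analyses, a multilevel approach will be used to consider different levels explored"; the levels then offered are assessment, student, center and country. The second says that for all parameters "the influence of the different centers and the level in the course (first or end years) will be investigated by regression analysis". Neither names experimental group as a term, and neither names an arm-by-score interaction.

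The practical assessment in the same section is handled differently: "These values will be compared between groups using multilevel analysis, considering both experimental groups and different centers". A joint model over both arms is therefore already part of the plan, but not for this analysis.

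On allocation, the Experimental Groups section says "The classes will be randomly divided into 2 groups", so students in both arms come from the same classes and centers. The ratio is not stated.

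**The concern.** Splitting by arm is a choice that the article states, not a detail it leaves open. The output will be two slopes, each with its own 5% test, printed side by side in the report of a randomized comparison. Many readers will compare them. If one is significant and the other is not, the natural inference is that laboratory training changes how knowledge or perception relates to detection skill. Two separate p-values cannot support that inference, because a difference in significance is not a test of a difference in slopes.

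Two separate fits also do not carry over into a sound comparison afterwards. The arms share centers and classes, and the standard error of an informal difference between the two slopes would ignore that sharing. Nor does the plan yield a single estimate of the association across all students, which for theory knowledge is a reasonable quantity to want.

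**Working it through.** The article gives no sample size, power or effect size for this analysis, so there is no figure of its own to reproduce. What follows is an illustration over a range of assumed values.

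**Inputs**
- From the article: two arms, one regression per arm, 5% level.
- Assumed: 1:1 allocation, two-sided tests, the same true slope and the same per-arm power *p* in both arms, independent students and independent tests. The assumed values of *p* are 30%, 50%, 80% and 90%.

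**Step 1: how often the two tests disagree although the slopes are equal**

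P(exactly one arm significant) = 2*p*(1 − *p*). P(trained arm only) = *p*(1 − *p*).

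| Per-arm power | Exactly one arm | Trained arm only |
|---|---|---|
| 30% | 2 × 0.3 × 0.7 = 42% | 21% |
| 50% | 2 × 0.5 × 0.5 = 50% | 25% |
| 80% | 2 × 0.8 × 0.2 = 32% | 16% |
| 90% | 2 × 0.9 × 0.1 = 18% | 9% |

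**Step 2: check by simulation** (5,000 runs per setting, equal slopes, no clustering)

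| Students per arm | Correlation | Per-arm power | Exactly one arm | Trained arm only |
|---|---|---|---|---|
| 100 | 0.2 | 52% | 49% | 24% |
| 200 | 0.2 | 81% | 31% | 16% |
| 500 | 0.1 | 61% | 48% | 24% |
| 500 | 0.2 | 99% | 1.2% | 0.5% |

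The simulated rates agree with the formulas. Over all settings run (50 to 500 students per arm, correlation 0.1 to 0.3), a test of the arm-by-score interaction gave a false difference in 4.2% to 5.8% of trials, as a 5% test should. The disagreement rate depends on per-arm power, not on arm size alone: at 500 per arm it is negligible for a correlation of 0.2 or more, but not for 0.1.

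**Step 3: what a joint model does to precision**

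Let each arm-specific slope have standard error *s*. With a full interaction:
- arm-specific slopes: standard error about *s*, nearly the same as in separate fits;
- arm-averaged slope: √(*s*² + *s*²)/2 = *s*/√2 = 0.707*s*, which is 29% smaller than a single-arm slope;
- difference between slopes: √(*s*² + *s*²) = 1.41*s*.

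The joint model therefore adds a test and a combined estimate. It does not sharpen the arm-specific slopes.

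**The case against.** The strongest reply is that the article plans no comparison of these associations between arms. It says only that the association will be examined within each arm. Where it wants an arm comparison (theory scores, detection performance, perception scores), it says so. No stated objective or hypothesis concerns whether training alters the link between knowledge or perception and skill. This stands: a reader might infer that the plan is set to conclude that the association exists only among trained students, but no sentence says this. The danger lies in how parallel results will be read.

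A second reply is that arm-specific slopes are a sensible target. This also stands, most clearly for perception: controls rate a lecture, while the test group also had a 90-minute laboratory class, so one common slope may have little meaning. The argument is weaker for theory knowledge, since all students attend the same theoretical class. It follows that the plan cannot be said to waste precision on the slopes it asks for.

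A third reply is that a journal article leaves model terms to a fuller document. That covers unstated detail, but here the article states the split itself, and its general sentences on levels, center and course level do not supply an arm term.

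Finally, with sixteen centers, large arms cannot be excluded, and disagreement between the tests may then be rare. That is possible, but the article gives no numbers from which to establish it.

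**Conclusion.** The point holds as a low-severity improvement to a supportive analysis. The separate regressions give valid within-arm slopes, but no valid test of a difference between them and no combined estimate. With equal true slopes, the separate tests would split between the arms in 18% to 50% of trials over per-arm powers of 30% to 90%, and would favor the trained arm alone in 9% to 25%. An interaction test would err in about 5%.

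These rates rest on equal arms, two-sided testing, independent students and independent tests, and on assumed per-arm power. Clustering by center would change them, and they become negligible once the arms are large for the strength of association at hand.

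Two stronger readings should not be drawn. The efficacy, cost and retention comparisons are not affected. The 29% reduction in standard error belongs to the arm-averaged slope alone, not to the arm-specific slopes that the plan requests.

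**What to change.** Replace the separate fits with one multilevel model over both arms, one for each predictor score (theory knowledge, perception). Include arm, score, arm-by-score interaction, baseline knowledge, willingness to learn, center and course level. Then:

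- report the arm-specific slopes from this model, each with a confidence interval;
- report the interaction with its confidence interval, and claim a difference between arms only from it;
- do not read a non-significant interaction as proof of equal slopes, since its standard error is about 1.41 times that of one arm's slope;
- for theory knowledge, also report the arm-averaged slope; for perception, keep to the arm-specific slopes, because the activity being rated differs by arm.

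The theory and perception scores are obtained after the allocated activity, so the arm coefficient in this model should not be presented as the effect of training. That remains the task of the planned between-group comparisons.

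The cost is a sentence or two in the plan. The data are the same, and the multilevel approach is already planned.
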